### Data collection procedures

#### Effect evaluation

*Survey data* are obtained through electronic questionnaires developed in the survey program Enalyzer. Data are collected during class under administration of staff from Oxford Research [48]. Questionnaires are available in both Norwegian written languages (Norwegian bokmål and Norwegian nynorsk). One class hour (45 min) are allocated to completion of questionnaires, but as far as possible it is facilitated for spending more time for students who need it.

*Registry data* are obtained from county or school registries. The county project coordinators retrieve and handle the registry data to ensure anonymity of students through unique ID numbers and encryption codes. When anonymised, Oxford Research links the registry data with survey data.

#### Process evaluation

The process evaluation builds on two rounds of qualitative interview studies and school visits in 12 schools (the COMPLETE intervention schools) encompassing 19 subdivisions. The studies are conducted in the spring of 2017 (completed) and of 2018. They encompass qualitative interviews, both individual and group interviews, with school leadership (headmaster), subdivision leaders (e.g. study program leaders), class teachers, resource groups for the DSP, student mentors (DSP), students in the DSP, the MHST (counsellors, school nurses, team coordinators) and students in the target group for MHST. Every study (both 2017 and 2018) encompasses approximately 120 interviews and includes around 300 different persons. Every interview has a duration of approximately one hour. Every school visit covers three days and includes both interviews and observation of common areas like the canteen, social zones, outdoor areas, administration area and the teacher common room. Specific interview guides are developed for the different target groups in the study. These are structured interview guides with follow-up questions. The aim of the interviews is to capture the experiences the schools have with the implementation of the two interventions.

All data are stored according to guidelines and requirements for safe storage of data in the University of Bergen storage, SAFE.

### Statistical analyses

Findings will be reported according to the CONSORT guidelines for cluster RCTs [49].

Descriptive statistics from intervention and control groups will be presented comparing means, medians or percentage as appropriate for primary and secondary outcomes, potential mediators like relatedness, competence and autonomy, and potential moderators, like gender, family socioeconomic status, and ethnic background.

Effectiveness analyses will first be conducted according to the intention-to-treat principle, and adjusted for the clustered nature of the data. Further effectiveness analyses will be conducted stratified by implementation degree. Analyses of the primary and secondary outcomes will be conducted using latent growth models, specifically, linear mixed effects models and logistic mixed effects models as recommended [50, 51], and alpha levels will be set at *p* ≤ .05. The role of moderators and mediators will be assessed in latent growth model frameworks appropriate for these purposes. Potential differences in intervention effects between subgroups will be investigated in secondary analyses. Missing data will be handled with multiple imputations or FIML depending on what is appropriate in each analysis.

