**Methods/Design:**

The COMPLETE RCT is aimed at youth in upper secondary school, grade 1 (age 15-16 years), and examines the effect of the combination of the DSP and the MHST; and the DSP only, compared with a comparison group on the following primary outcomes: student completion, presence, average grade, and self-reported mental health. Seventeen upper secondary schools from four counties in Norway were randomized to one of the three arms: 1) DSP and MHST; 2) DSP; and 3) comparison (offered DSP intervention in 2018/2019). The study will evaluate the interventions based on information from two cohorts of students (cohort 1 (C1) and cohort 2 (C2)). For C1, data was collected at baseline (August 2016), and at first follow-up seven months later. Second follow-up will be collected 19 months after baseline. For C2, data was collected at baseline (August 2017), and first and second follow-up will be collected similarly to that of C2 seven and 19 months respectively after baseline. Process evaluations based on focus groups, interviews and observation will be conducted twice (first completed spring 2017).

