### Sample

The size of the sample was based on two prerequisites. First, the implementation of the program in the intervention schools required training of several stakeholder groups. The NGO delivering the universal program set an upper limit to 12 secondary schools which would be manageable for them. Also, in further decisions on sample size, the power calculations with hierarchical structured data [28] followed the procedure applied in a prior comparable psychosocial intervention in Norwegian schools [29]: A hierarchical structure with students in class, a significance level of *p* ≤ .05, power of .80, classes with an average of 20 students, an assumed intraclass correlation of 0.05, and a minimum expected effect size of 0.25 on primary and secondary outcomes (expected effect sizes (Cohens *d*) in similar studies lies between .20 and .50, see meta analyses by Durlak et al. (2011). These power calculations indicated that a sample of 975 students and 49 classes was needed to detect a small effect size of .25.

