### Randomization of schools

Representatives from Oxford Research who had no prior knowledge of the recruited schools allocated schools to the intervention or control groups according to a computer generated randomization list. To ensure an equal balance of intervention and control groups in each county, stratified randomization was practices in which schools were stratified by county. All schools were given a random number ranging from 0 to 1 by using a randomisation command in the statistics software of Stata 14. Stata generated a random number based on a chosen key. Next, the schools were sorted after the size of the random number in each stratum. The school with the highest number was appointed to the intervention group 1 – I1 (DSP only), the school with the second to highest number was appointed to intervention group 2 – I2 (DSP and MHTS), and the school with the third to highest number was appointed to the control group – C. This procedure was repeated until all schools in each stratum were appointed to a group.

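### Schools were randomised within county, but the only hierarchy the article names is students in class; the analysis section should name school as a level, include county, and use small-sample inference for 17 schools

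*Protocol article*

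**What the plan says.** All references are to the protocol article.

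- **Unit of randomisation** (abstract, Methods/Design): "Seventeen upper secondary schools from four counties in Norway were randomized to one of the three arms".
- **Strata and allocation** (Randomization of schools): "stratified randomization was practices in which schools were stratified by county". Within each county, schools were sorted by a random number and assigned in the fixed order I1, I2, control. "This procedure was repeated until all schools in each stratum were appointed to a group".
- **Hierarchy named** (Sample): "A hierarchical structure with students in class", with 20 students per class and an intraclass correlation of 0.05. This describes the power calculation.
- **Effect analysis** (Statistical analyses): "Effectiveness analyses will first be conducted according to the intention-to-treat principle, and adjusted for the clustered nature of the data". The models are latent growth models, in linear and logistic mixed-effects form, at a 5% level. "Missing data will be handled with multiple imputations or FIML depending on what is appropriate in each analysis".

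The analysis section does not name a clustering level, a county term, an estimator, or a reference distribution for the tests.

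**The concern.** In a school-randomised trial, the error of a treatment contrast is driven by variation between schools, and there are only 17 of them. A model that clusters by class treats the classes of one school as independent once arm is accounted for, and so understates that error. A model with a school effect can still understate it if the variance is estimated by maximum likelihood and tested against a normal distribution. In either case a false claim of benefit becomes more likely than 5% on each affected outcome.

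County is a separate matter. It was a stratification factor, and the fixed allocation order gives unequal county shares across arms. An analysis without county leaves that imbalance in the estimate and gives up the precision that stratification was meant to buy.

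**Working it through.** **1. The plan's own figure.** Inputs from Sample: d = 0.25, alpha 0.05 (two-sided, which reproduces the figure), power 0.80, 20 per class, ICC 0.05.
- n per arm for two means: 251.2, rounded up to 252.
- Design effect for classes: 1 + (20 − 1) × 0.05 = 1.95.
- Two arms: 2 × 252 × 1.95 = 983 (979.5 unrounded); 983 / 20 is about 49 classes.

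The article states 975 students and 49 classes. The figure therefore reproduces with clustering by class only and no school variance.

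**2. If the same hierarchy were used in the effect model.** Each cohort has about 3003 / 17 = 177 students per school (Recruitment of schools), or about 9 classes of 20, taken as 180. Hold the total within-class correlation at 0.05 and let ρ be the part shared across a school (an assumption; the article gives no school ICC):

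Design effect = 1 + 19 × 0.05 + (180 − 20) × ρ = 1.95 + 160ρ

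| ρ (assumed) | Design effect | True SE / class-only SE | Type I error, 2 × [1 − Φ(1.96 / ratio)] |
|---|---|---|---|
| 0 | 1.95 | 1.00 | 0.050 |
| 0.01 | 3.55 | √(3.55/1.95) = 1.35 | 0.146 |
| 0.02 | 5.15 | √(5.15/1.95) = 1.63 | 0.228 |

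Two separate simulations gave 0.148 and 0.152 at ρ = 0.01, and 0.232 and 0.240 at ρ = 0.02. Pooling both cohorts (about 18 classes per school) would make this worse, because the number of schools stays at 17.

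**3. School effect included, estimator uncorrected.** Maximum likelihood divides the between-school sum of squares by 17 instead of by the residual degrees of freedom. A z test at 1.96 is then a t test with too low a cut-off:
- Three arm parameters, 14 df: cut-off 1.96 × √(14/17) = 1.779; type I error 0.097.
- Three county terms added, 11 df: cut-off 1.96 × √(11/17) = 1.577; type I error 0.143.

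Simulation at ρ = 0.02 (arms 6/6/5 assumed) agrees: 0.097 and 0.142. REML with z gives 0.071 and 0.077. A t reference on 14 or 11 df gives 0.052 and 0.050.

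**4. County left out when counties differ.** With ρ = 0.02 and an assumed county variance of 0.01 to 0.02, the t test on 14 df has type I error 0.032 to 0.024. The mean model SE is 0.115 to 0.127 against a true 0.104 to 0.106. The error bars are too wide.

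**5. Precision from including county.** For 6 against 5 schools, SE = √[design effect / 180 × (1/6 + 1/5)], and the minimum detectable effect at 80% power is about (t at 0.975 + t at 0.80) × SE.
- ρ = 0.02, no county, 14 df: SE 0.102; (2.145 + 0.868) × 0.102 = 0.31.
- County explains 25% of the school variance (ρ = 0.015, 11 df): SE 0.094; (2.201 + 0.876) × 0.094 = 0.29.
- County explains 50% (ρ = 0.01, 11 df): SE 0.085; 3.077 × 0.085 = 0.26.

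The 25% to 50% range is an assumption.

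**6. What the allocation order does.** The process evaluation section gives 12 intervention schools, so 5 are controls. Each complete triple within a county yields one control, so there are 5 triples (15 schools) and 17 − 15 = 2 leftover schools. Leftovers take the I1 and I2 places first and never reach control. Either one county has both (arms 6/6/5) or two counties have one each (7/5/5). County sizes are not in the text. With sizes 3, 3, 5 and 6 as an illustration, the 5-school county supplies 2/6 = 33% of each intervention arm and 1/5 = 20% of controls.

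**The case against.** The strongest reply is that the article does not describe a faulty model.

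- **Class-only analysis.** A reader might infer that the effect model clusters by class alone. The documents do not say so. The students-in-class wording belongs to the power calculation. The analysis section promises adjustment for clustering without naming or excluding a level, the article calls the trial a school-based cluster RCT, and it commits to CONSORT for cluster trials. This stands: the 15% to 23% is conditional.
- **Maximum likelihood with z tests.** A reader might infer this from the growth-model framework and FIML. FIML appears only as one of two options for missing data, and linear mixed models can be fitted by REML with t tests. This also stands.
- **County.** A reader might think that omitting county makes error bars too small, or that the article decided to omit it. Step 4 shows the opposite direction, and the section lists no model terms at all. In the illustrative county split, the imbalance has an SD of about 0.16 times the county SD, or about 0.02 SD at county variance 0.01 to 0.02, which is small against a target of 0.25.
- **Single time point.** For arm-by-time effects on survey outcomes with a baseline, stable school differences largely cancel and school-by-time variance is what counts. This limits how far the figures transfer to those outcomes. It helps less for completion, absence and grades, whose registry data are collected after grades 1, 2 and 3.
- **Scope.** Model terms, estimator and degrees of freedom are often left to an analysis plan, so silence alone is no fault. What remains is that the one hierarchy the article does define sits below the randomised unit, and nothing in it shows that the analysts would use school.

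**Conclusion.** The point holds as a conditional risk with a cheap remedy. The article randomises schools within county, defines only a class hierarchy, and fixes mixed and growth models for 17 schools without saying how school enters.

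- Carrying the class hierarchy into the analysis would give a type I error of about 15% to 23% at school ICC 0.01 to 0.02.
- A school effect with uncorrected maximum likelihood and z tests would give about 10%, or about 14% with county terms.
- Leaving out county is a loss of precision and an uncorrected, probably small, imbalance. It is not a source of false positives through small standard errors.

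These sizes rest on assumed school ICC and county variance, 9 equal classes of 20 per school, arms of 6/6/5, one cohort, and a continuous outcome at one time point. The article does not establish that either inflated analysis is planned.

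**What to change.** In the Statistical analyses section, or in the analysis plan it relies on, state for every primary and secondary contrast:

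1. School, the randomised unit, is a cluster level, with class within school and student for repeated measures. Growth models also allow school-by-time variance; random intercepts alone would not protect arm-by-time tests.
2. County is a fixed effect.
3. Inference uses school-level degrees of freedom: REML with Kenward-Roger for continuous outcomes. For binary outcomes, use a county-adjusted school-level analysis or a within-county permutation test that follows the allocation rule actually used.

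Items 2 and 3 must be adopted together, because county terms under maximum likelihood with z tests worsen the error rate. The work is wording and minor programming. The price is wider intervals and 3 school-level degrees of freedom spent on county (14 down to 11).

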### Baseline assessment and follow up

Each student cohort will be assessed through survey on three (C1) or two (C2) occasions (Figs. 2 and 3):Baseline: during the first or second week of school in the first semester of grade 1C1: August 2016 (already completed)C2: August 2017 (already completed)First follow-up: in the second semester of grade 1C1: March 2017 (already completed)C2: March 2018Second follow-up: in the second semester of grade 2C1: March 2018

Registry data on drop-out, absence and school grades after grade 1, 2 and 3 will be linked to survey data. In addition, survey data from grade 1 teachers of the C2 will be collected in August 2017 and March 2018, to assess any change in teacher perceptions on their relational competence over the intervention period. However these data will be considered supplemental and not part of the quantitative effect evaluation.

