### Intervention

Schools in the intervention groups (I1 and I2) started the planning of intervention implementation in the spring of 2016, and C1 students in the intervention schools received the interventions immediately after semester start in August 2016. The same procedure will be followed for the C2 students, starting upper secondary school in August 2017. Schools in the control group will be offered the DSP after completion of the second intervention year, starting in August 2018.

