### Trial status (01.11.2017)

The COMPLETE study is mid-way in its project period with three out of five student survey data collections completed, one out of two process evaluations completed, and one out of five linking of registry data on primary outcomes completed. The first report to the Norwegian Ministry of Education is due in January 2018, and the final project report is due in December 2019.

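### Latent growth models are assigned to every outcome with no effect parameter named, and a growth term does not suit C2 wellbeing, absence and grades, or dropout

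*Protocol article*

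**What the plan says.** Under Statistical analyses, the protocol article gives one model family for all effectiveness outcomes: "Analyses of the primary and secondary outcomes will be conducted using latent growth models, specifically, linear mixed effects models and logistic mixed effects models". It names no slope, group-by-time term, random slope or time point as the treatment effect.

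Other sections fix the data these models would receive.

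- **Survey waves.** Under Baseline assessment and follow up: "Each student cohort will be assessed through survey on three (C1) or two (C2) occasions". The listed dates give C2 August 2017 and March 2018 only. Trial status agrees, with "three out of five student survey data collections completed". The abstract differs; of C2 it says that "first and second follow-up will be collected similarly to that of C2 seven and 19 months respectively after baseline".
- **WEMWBS.** Table 3 lists it among the primary outcomes, from the C2 student survey alone. SCL-5 comes from both cohorts.
- **Registry outcomes.** Absence, grades and dropout are taken after each school grade, while "C1 students in the intervention schools received the interventions immediately after semester start in August 2016", with the same procedure planned for C2 in August 2017.
- **Dropout.** Table 3 defines it as non-completion within five years, or having quit with no regular activity during the study. The same row defines completion of a school year, which is scored every year.

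**The concern.** A latent growth model describes change over repeated measurements, and its characteristic parameter is the slope. That is informative when the first measurement precedes the intervention, when there are enough waves to separate slope variation from residual error, and when the outcome can move over time. Each condition fails for at least one primary outcome here.

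Since the plan does not say whether the effect is a level difference or a slope difference, an analyst who follows the words latent growth model could take the slope. For absence and grades, that would measure change after the first year of exposure and leave out whatever the programme achieved in that year. Leaving level or slope open across four primary domains and two intervention arms also allows the choice to be made after the results are seen.

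**Working it through.** **1. The plan's own sample size.** Inputs from the Sample section: "power of .80, classes with an average of 20 students, an assumed intraclass correlation of 0.05". The smallest difference to be detected is given there as d = 0.25. Statistical analyses says "alpha levels will be set at" 0.05; I assume two-sided.

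- Per group: 2 × ((1.960 + 0.842) / 0.25)² = 251.2.
- Design effect: 1 + (20 - 1) × 0.05 = 1.95.
- Two groups: 2 × 251.2 × 1.95 = 979.5 students, or 979.5 / 20 = 49.0 classes.

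The plan states 975 and 49, so the figure reproduces. The calculation behind it is a two-group comparison at one time point, which is a level difference.

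**2. How many C2 survey waves.** By 1 November 2017 three rounds were complete: C1 August 2016, C1 March 2017 and C2 August 2017. C1 March 2018 and C2 March 2018 make five. A 19-month C2 wave would make six. The schedule and the trial status therefore agree on two waves, and the abstract conflicts with both.

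**3. Identification with two waves.** At times 0 and t, with intercept variance a, covariance b, slope variance c and residual variance e:

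- Var(Y0) = a + e
- Cov(Y0, Yt) = a + bt
- Var(Yt) = a + 2bt + ct² + e

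That is three equations in four unknowns. A numerical rank check gave 3 for 4 parameters. Counting means as well, there are 5 moments for 6 parameters (7 if the residual variance differs by wave). With three waves there are 9 moments for 6 to 8 parameters, and the model is identified.

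A random-intercept model needs only 4 parameters per arm. In 30 simulated two-wave data sets of 1,000 students, its group-by-time term averaged 0.257 for a true 0.25.

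C2 is followed to the end of grade 2, so its absence and grade series also have two values if C2 is analysed alone.

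**4. Absence and grades: slope against level.** The documents give no effect profile over grades 1 to 3, so I take three assumed ones in SD units. With equally spaced years, slope = (year 3 - year 1) / 2.

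| Assumed benefit, grades 1 / 2 / 3 | Slope difference per year | Level difference at end of grade 1 |
|---|---|---|
| 0.25 / 0.25 / 0.25 | 0.00 | 0.25 |
| 0.25 / 0.20 / 0.15 | -0.05 | 0.25 |
| 0.25 / 0.30 / 0.35 | +0.05 | 0.25 |

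Under the first profile, a slope test rejects only at its alpha level.

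**5. Dropout.** Assume a control hazard of 5% per year.

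- Intervention hazard 3% in every year: the log odds ratio of the yearly hazard is -0.53 each year, with slope 0.00.
- Intervention hazard 3% in year 1 only, then 5%: three-year dropout is 1 - 0.97 × 0.95² = 12.5%, against 1 - 0.95³ = 14.3%. The cumulative log odds ratio runs -0.53, -0.24, -0.16. Its slope is (-0.16 + 0.53) / 2 ≈ +0.19, pointing towards harm although the intervention arm has fewer dropouts.

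**6. Where growth is identified.** SCL-5, school satisfaction and loneliness have three C1 waves. Even there a straight line is approximate: an effect of 0.25 at both 7 and 19 months gives a fitted slope of 0.0117 per month, which is a change of 0.08 by month 7 and 0.22 by month 19.

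**The case against.** The strongest reply is that the sentence narrows latent growth models to linear and logistic mixed models and states no slope contrast and no random slope. This stands. In the profiles above, the same model class returns a level difference of 0.25. Randomisation means that a level comparison of grades or absence needs no pre-intervention value. A random-intercept model handles two-wave WEMWBS. Both a fixed-date dropout status and a discrete-time hazard can be fitted as logistic mixed models. Yearly completion can be modelled repeatedly without difficulty.

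A reader might therefore infer too much: that the planned analysis cannot estimate the effects, or that the trial will report none. The documents do not support that. Inability to estimate holds only for a random-slope model at two waves, and missing the effect holds only if the slope is taken as the effect.

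It can also be said that choosing a contrast belongs in an analysis plan that is not shown. That is fair for the contrast alone. It does not cover the sentence itself, which assigns growth models to every primary and secondary outcome, including those for which growth is the wrong description. Nor does it cover the conflict over C2 waves, which lies within the article. If the abstract is right on C2, the identification point for WEMWBS falls away; the points on registry outcomes and dropout remain.

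**Conclusion.** The point holds in conditional form. The article prescribes a growth-model family for all outcomes and leaves the effect parameter unnamed, and growth is unidentified, misdirected or ill-suited for named primary outcomes:

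- **WEMWBS:** the random-slope growth model is not identified if C2 has two waves, as the schedule and trial status indicate.
- **Absence and grades:** a slope contrast gives 0.00 for a constant benefit of 0.25 SD and the wrong sign for a fading one.
- **Dropout:** a trajectory does not describe a one-time status, and its slope can point the wrong way.

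The survey outcomes with three C1 waves and yearly completion are not affected in this way. The sizes rest on assumed effect profiles and hazards; the moment count does not. Naming a level difference would also match the comparison that reproduces the sample size. This should be changed, but it does not make the trial's data unusable.

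**What to change.** State the primary contrast as the adjusted arm difference at a named time, within the mixed models already named.

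- **Survey scores (SCL-5, WEMWBS, secondary scales):** follow-up score on arm, August score, county, and cohort where both contribute, with school and class effects. Adjusting for the August score also has lower student-level variance than analysing change: 1 - r² against 2(1 - r). That is 0.64 against 0.80 at an assumed correlation of 0.6, 0.75 against 1.00 at 0.5, and 0.51 against 0.60 at 0.7. This is a gain in efficiency, not the reason for the change.
- **Absence and average grade:** level at the end of a named school year.
- **Dropout:** cumulative status at a fixed date, or a discrete-time hazard fitted as a logistic mixed model. Yearly completion may stay as a repeated binary outcome.
- **Growth curves:** secondary, for C1 survey outcomes with three waves.
- **C2 waves:** reconcile the abstract with the follow-up schedule and the trial status.

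The cost is analysis wording, plus one sensitivity analysis without the August score, because that survey falls in the first or second week of school, when exposure has begun. At the stated status date one of five registry linkages and three of five surveys were complete, so the change should be dated and recorded.
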